## 14.2 Analysis of Secondary Endpoints

Furthermore, A mixed model ANOVA will be used to evaluate possible differences in symptoms, HRV, BPV, cognitive performance and blood biomarkers between the standard of care group and AE intervention group (between group analysis) across 6 time points; 7, 14, 21, 28, and 90 days post-SRC (within group analysis). If the data fails the required normality assumption, the appropriate transformation will be performed on all data. We expect approximately 40% females in our study sample, allowing for differential responses between males and females. We will perform separate Kaplan Meier analyses in males and females on time to medical clearance between the standard of care and AE intervention groups. Likewise, we will perform separate mixed model ANOVA analyses in males and females to evaluate differences between AE intervention and standard care groups for all aforementioned secondary measures.

Regarding blood biomarker analysis, each individual biomarker will only be included for statistical quantitation if they fall within the lower and upper limits of quantitation (LLOQ and ULOQ, respectively) as delineated by the manufacturer. All samples will be run in duplicate, and excluded if the coefficient of variance (CV) between duplicate samples is > 25%. Furthermore, mean statistical analysis will only be performed on biomarkers that have quantifiable samples in > 50%, in all groups in question. A quantifiable sample is 1) within the manufacturers quantitative range, and 2) displays a CV between duplicates of < 25%. In instances where one or both groups contain <50% quantifiable samples, differences between these groups will be evaluated by χ^2^.

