### 9.6.3 Assessments at Day 7, 14, 21, 28, and 90:

***HRV Assessment:*** Resting HRV will be based on variability in participants’ R-R intervals using the Polar heart rate V800 sports watch and corresponding chest strap heart monitor (Polar ®, QC, Canada). The research team will be able to extrapolate the ratio of low frequency (i.e. sympathetic activity) to high frequency (i.e. vagal activity) signals that appear on a beat-to-beat basis, per subject. Participants will be asked to lie down in the supine position to allow for set up and accommodation. HRV will be assessed for 5 minutes in the supine position, then, after a 1-minute accommodation period, a final 5 minute HRV assessment in the upright-seated position will be performed.

***BPV Assessment****:* BPV will be assessed non-invasively on a beat-to-beat basis using the Finapres NOVA figure cuff device (Finapres Medical Systems, Amsterdam, Netherlands) employing a similar protocol to the assessment of HRV; participants will undergo a 5 minutes accommodation period, at which point their BPV will be assessed for 5 minutes in the supine position. Following this, participants will be asked to assume an upright-seated position, followed by a one-minute accommodation period and an additional five-minute assessment period in the upright-seated posture. Time and frequency domain measures of BPV will be recorded and digitally uploaded for each posture (not including the accommodation periods), as well as throughout the transition from one posture to the next, in order to determine the balance of sympathetic versus parasympathetic influence on the ANS.

***Blood Samples:*** Peripheral blood samples (approximately 20 mL) will be drawn from participants by a trained phlebotomist. Blood will be drawn on days 7, 14, 21, 28, 90 and 180 days post-injury in both groups, but before the onset of exercise in the SAEP intervention group. Specimens will be immediately centrifuged to isolate the plasma/serum, and aliquots will be stored at -70^ο^C until subsequent analysis. High sensitivity multiplexed immunoassay will be employed to quantitate inflammatory cytokines and chemokines, and CNS-injury specific biomarkers. In addition, radioimmunoassay will be employed to evaluate numerous neuroendocrine hormones.

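### Section 14.2's mixed model ANOVA, read as a split-plot analysis, loses every participant with a missing visit; for biomarkers, the protocol's own sample exclusions could make that loss large

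*Protocol*

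**What the plan says.** Protocol section 14.2 gives one method for all repeated measures: "A mixed model ANOVA will be used to evaluate possible differences in symptoms, HRV, BPV, cognitive performance and blood biomarkers". Arm is the between-group factor and visit the within-group factor, "across 6 time points; 7, 14, 21, 28, and 90 days post-SRC (within group analysis"). A transformation is foreseen if normality fails. The method is repeated by sex: "we will perform separate mixed model ANOVA analyses in males and females".

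The same section sets three rules for biomarkers:
- Range: "each individual biomarker will only be included for statistical quantitation if they fall within the lower and upper limits of quantitation".
- Precision: a sample is "excluded if the coefficient of variance (CV) between duplicate samples is > 25" per cent.
- Entry to a comparison of means: "mean statistical analysis will only be performed on biomarkers that have quantifiable samples in > 50%, in all groups in question". Below that share, a chi-squared comparison is used.

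Section 14.2 does not say what happens to a participant who has some visits but not all. Section 9.6.3 adds a sixth blood draw: "Blood will be drawn on days 7, 14, 21, 28, 90 and 180 days post-injury in both groups".

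**The concern.** A split-plot ANOVA works on complete participants, whereas the biomarker rules work on single samples. A marker can therefore pass the 50% rule although few participants have a usable value at every visit. The comparison of means would then rest on a small subset. It would also be a selected one if missed visits or unusable samples relate to recovery.

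Other sources of missing data are foreseen. Section 7.0 lets blood collection end when a vein cannot be accessed, and section 14.1 expects attrition. The stakes are not only secondary: sections 2.0 and 9.0 list symptom scores as a primary outcome measure, and 14.2 analyses symptoms with this method.

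**Working it through.** **Inputs from the protocol.** 53 per group (section 13.0); five listed visits, about 40% females, and a mean analysis allowed above 50% quantifiable (section 14.2). The protocol gives no missing-data rate and no sample size for the repeated-measures analyses, so there is no figure of its own to reproduce here. The 53 serves only as a denominator; how it was derived is a separate matter.

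**Assumptions.** q is the share of participants with a usable value at a given visit, equal across visits. Every q and every correlation below is assumed.

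**Step 1: complete cases, independent missingness.** Share complete = q^5; number per arm = 53 × q^5. For example, 0.80^5 = 0.328 and 53 × 0.328 = 17.4.

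**Step 2: clustered missingness.** A visit is usable when a latent normal variable passes a cut-off set by q. The latent variables of one person correlate 0.5 across visits, and the share complete at all five is computed numerically.

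**Step 3: a model using all available visits.** This uses generalised least squares information for a saturated arm-by-visit model, with values missing completely at random and independently, compound symmetry, and a within-person correlation of 0.5. The effect is averaged over visits. The standard-error ratio is the square root of (effective n ÷ complete cases from Step 1); at q = 0.80, √(50.3/17.4) = 1.70.

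| q | Complete, independent | Per arm | Complete, latent correlation 0.5 | Per arm | Effective n per arm, all visits used | SE ratio |
|---|---|---|---|---|---|---|
| 0.95 | 77% | 41.0 | 83% | 44.1 | 52.4 | 1.13 |
| 0.90 | 59% | 31.3 | 71% | 37.5 | 51.8 | 1.29 |
| 0.80 | 33% | 17.4 | 51% | 27.2 | 50.3 | 1.70 |
| 0.70 | 17% | 8.9 | 37% | 19.4 | 48.4 | 2.33 |
| 0.51 | 3.5% | 1.8 | 17.5% | 9.3 | not computed | not computed |

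**Step 4: where most of the sample is lost.** Under independence, q^5 < 0.5 when q < 0.5^(1/5) = 0.871. With six draws the limit is 0.5^(1/6) = 0.891.

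**Step 5: the 50% rule.** At q = 0.51, latent correlations from 0.3 to 0.9 leave 11% to 36% complete. Whatever the clustering, the complete share cannot exceed q, so it cannot exceed 51%.

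**Step 6: consequences at q = 0.80, independent missingness.** The standardised difference detectable with 80% power is 2.8016 × √(2 × 0.6/n), where 0.6 = (1 + 4 × 0.5)/5 is the variance of a five-visit mean. It is 0.74 for complete cases (n = 17.4), 0.43 when all visits are used (n = 50.3) and 0.42 with full data (n = 53). For day 90 alone, the effective n is 45.7 per arm against 17.4. In the female analysis, 53 × 0.40 = 21.2 per arm falls to about 6.9 complete.

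**The case against.** The strongest objection is that 14.2 states no complete-case rule and names no estimation method. Mixed model can mean a linear mixed model, and the between and within labels may only name its factors. Estimation details are also ordinary content for a statistical analysis plan, which is not shown. This stands in part: deletion is inferred from the method's name. It does not remove the point, because the protocol does name a method. Its most natural reading fits badly with the exclusion rules beside it, and the clearer wording does no harm if a linear mixed model was always meant.

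Three stronger readings are tempting, and the protocol does not support them:
- **All secondary comparisons would rest on a small subset.** The assay exclusions apply only to biomarkers. The other outcomes lose data through missed visits, whose rate is unknown; at 95% availability 77% of participants are complete.
- **About two participants per arm would remain.** This takes the 50% entry rule as an expected rate and assumes independence. It is a minimum for entry, and persistent low levels or dropout plausibly cluster in the same people.
- **A likelihood-based model would remove the bias.** It is valid under missing at random. Values outside the assay range are missing because of their size, and data discarded at withdrawal (section 11.0) are beyond any model.

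It is also fair to say that Step 3 assumes a known compound-symmetric covariance. An estimated unstructured one would gain somewhat less and could be hard to fit in the smaller analyses.

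**Conclusion.** The point holds conditionally and is worth acting on. If 14.2 means a split-plot ANOVA, any participant with a missing visit is lost. For biomarkers the loss could be large, since a marker just above the 50% rule keeps at most about half of the participants as complete cases, and probably far fewer. For the other outcomes the size cannot be given from the protocol.

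Under independent missingness, complete cases run from 41 per arm at 95% availability to 9 at 70%, and fall below half the sample only under about 87%. Clustering softens this. A model using all available visits would recover most of the lost precision if values are missing at random, but would not by itself deal with out-of-range values.

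Separately, 14.2 announces six time points and lists five, while section 9.6.3 schedules six blood draws. These passages must be reconciled, since the number of visits defines the model.

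**What to change.** In section 14.2:
- Replace mixed model ANOVA with a likelihood-based linear mixed model for repeated measures that uses all available visits, with arm, visit as a category, and arm by visit.
- Name a simpler covariance structure as fallback for the sex-specific and sparse-biomarker analyses.
- For the symptom analysis, add the Day 3 PCSS as a covariate; section 9.1 already collects it.
- Treat biomarker values below the lower or above the upper limit of quantitation as censored at that limit rather than dropping them.
- Reconcile the stated six time points with the five visits listed, and both with the day-180 draw in section 9.6.3.

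The cost is a few sentences and a little more analysis work, mainly for the censored values. No new data are needed. Data discarded at withdrawal stay lost.

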# 13.0 SAMPLE SIZE

Sample size was determined from a power analysis incorporating published data by our group on days to medical clearance in high school patients evaluated at the MacIntosh Clinic (mean time to clearance = 43 days, SD = 20 days).^79^. Hence, to reduce time to medical clearance to 36 days (delta = 7), at a significance level of 0.05 and a at a moderate effect level (0.7), would require 53 participants per group.

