# 14.0 DESCRIPTION OF STATISTICAL METHODS

## 14.1 Analysis of Primary Endpoints

We will statistically evaluate time to medical clearance between the standard of care and AE intervention groups by Cox regression (or proportional hazards regression). This approach allows one to control for the effect of several variables (i.e., sex/gender, age, initial PCSS), while evaluating a single outcome measure. Furthermore, we have the ability account for censor subjects who are removed from the study due to exercise-induced symptom exacerbation or attrition.

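### The separate male and female analyses in section 14.2 neither test nor estimate whether the treatment effect differs by sex; an exploratory treatment-by-sex interaction should be added

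*Protocol*

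**What the plan says.** Section 14.2 of the protocol introduces sex with this sentence: "We expect approximately 40% females in our study sample, allowing for differential responses between males and females". Two methods follow. For time to clearance: "We will perform separate Kaplan Meier analyses in males and females on time to medical clearance". For the other measures (symptoms, HRV, BPV, cognition, blood biomarkers): "we will perform separate mixed model ANOVA analyses in males and females to evaluate differences between AE intervention and standard care groups". Both compare exercise with usual care inside one sex at a time.

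In section 14.1 sex appears only in the list of variables that the primary Cox model controls for: "sex/gender, age, initial PCSS". The protocol contains no treatment-by-sex term and no other formal comparison of the male effect with the female effect.

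The aims and hypotheses in section 8.0 do not mention sex.

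**The concern.** A within-sex analysis asks whether exercise beats usual care in that sex. Whether the benefit differs between the sexes is another question, and it needs the difference between the two effects with its standard error. Neither planned analysis gives that.

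The split also invites a known misreading. If one sex reaches p < 0.05 and the other does not, the pair looks like evidence of a differential response, although this happens often when the effects are equal. The expected male group is half as large again as the female group (60% against 40%), so for the same effect males reach significance more easily. The trial could then be read as showing that exercise helps one sex only. The split is repeated for every secondary measure, which gives further chances for such a contrast.

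This is not a detail left to an analysis plan, because the protocol itself names the method.

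**Working it through.** **Inputs**
- Section 13.0: "mean time to clearance = 43 days, SD = 20 days"; target 36 days, a difference of 7 days or 7/20 = 0.35 SD; 53 per group, 106 in total; "at a significance level of 0.05" (taken as two-sided).
- Section 14.2: 40% female.
- Assumed, because the protocol does not give them: equal allocation within each sex, SD 20 in females as well as males, no dropout.

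**The plan's own figure.** The protocol gives no figure for the analyses by sex. Its 53 per group does not follow from 7 days and SD 20: n = 2 × (1.96 + 0.84)² × (20/7)² gives 129 per group at 80% power, and 53 per group gives 44%. That is a separate problem. Here 106 is used only as the planned size.

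**Group sizes per arm.** Females 0.4 × 106/2 = 21.2; males 0.6 × 106/2 = 31.8.

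**Power within each sex**, Φ(d/√(2/n) − 1.96) with d = 0.35:
- Females: 0.35/√(2/21.2) = 1.14; power 0.206.
- Males: 0.35/√(2/31.8) = 1.40; power 0.286.

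**Chance that exactly one sex is significant when the true effects are equal**, pF(1 − pM) + pM(1 − pF):
- 0.206 × 0.714 + 0.286 × 0.794 = 0.147 + 0.227 = 0.374.
- In 20,000 simulated trials with t-tests (21 and 32 per arm), power was 20% and 28%, and exactly one sex was significant in 37%.

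**Other assumptions, same formula**

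| True effect, equal in both sexes | Power, females | Power, males | Exactly one significant |
|---|---|---|---|
| None | 5% | 5% | 9.5% |
| 0.35 SD (7 days) | 21% | 29% | 37% |
| 0.544 SD (80% power overall) | 43% | 58% | 51% |
| 0.7 SD (14 days) | 63% | 80% | 43% |
| Log-rank, hazard ratio 0.7 | 21% | 30% | 38% |
| Log-rank, hazard ratio 36/43 | 8% | 11% | 17% |

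The log-rank rows use Φ(√D × \|ln HR\|/2 − 1.96) with D = 42.4 and 63.6 events, that is, everyone cleared. The ratio 36/43 treats clearance times as exponential, which fits a mean of 43 and SD of 20 poorly. The 0.7 SD row is one reading of the unclear 0.7 in section 13.0 and is not the protocol's stated difference. Simulated rates at 11 and 14 days were 52% and 44%.

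**Interaction test instead**
- False sex difference at two-sided 0.05: 5.0% in simulations with a common effect of 0, 7, 11 or 14 days.
- Standard error in mean days: 20 × √(2/21.2 + 2/31.8) = 7.93, against 20 × √(2/53) = 3.89 for the overall effect, 2.04 times as large.
- Power for a 7-day difference in effect: Φ(7/7.93 − 1.96) = 0.14. For 14 days: 0.42. For 80% power: 7.93 × (1.96 + 0.84), about 22 days.
- On the Cox scale the interaction is a ratio of hazard ratios. If everyone is cleared, the standard error of its logarithm is √(4/42.4 + 4/63.6) = 0.40, and exp(1.96 × 0.397) is about 2.2. The 95% interval therefore runs about a factor of 2.2 either way.

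**The case against.** The strongest reply is that section 14.2 can be read as a plan to report results by sex and nothing more. It never says that a sex difference will be declared when one sex is significant and the other is not. This stands, so the 37% is conditional: it applies only if someone compares the two p-values. What remains is that the section gives differential response as the reason for the split and offers no analysis that addresses it.

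The figures also rest on choices the protocol does not make. They use mean days with full follow-up, whereas the planned outcome is censored time to clearance. The SD comes from reference 79, whose title describes male high school students, and the protocol gives no female SD. Hence the range of 17% to 51%.

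It is also true that an interaction test has little power here. That limits what can be learned from 106 participants under either approach; the interaction interval at least shows it.

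Three stronger readings are tempting but not supported:
- That the trial leaves a formal sex hypothesis unanswered. Section 8.0 poses none.
- That the Kaplan-Meier comparisons are invalid because they drop the Cox covariates. Within a sex only age and initial PCSS are lost, and an unadjusted comparison of randomised arms remains valid; the cost is mainly precision.
- That the primary result is at risk. The Cox comparison in section 14.1 does not depend on the split.

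**Conclusion.** The point holds in a limited form. The protocol gives differential response by sex as the reason for an analysis that cannot show it. If the within-sex p-values are compared, equal true effects would leave exactly one sex significant in about 37% of trials at the protocol's 7 days and SD 20, and in 17% to 51% under the other non-null assumptions tried, against 5% for an interaction test. These figures assume about 21 females and 32 males per arm, equal allocation within sex, a common SD of 20 and no dropout; dropout would lower within-sex power further. They concern time to clearance. The same reasoning applies to the secondary measures, but the protocol gives no SDs from which to compute a rate for them.

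A reader might infer that an interaction test would settle whether the sexes respond differently. At this sample size it probably would not: it is the valid estimate, but an imprecise one.

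**What to change.** - In the Cox model of section 14.1, fit an exploratory version with treatment, sex, treatment-by-sex, age and initial PCSS. Report the ratio of hazard ratios with its 95% interval, and take the sex-specific hazard ratios from the same model.
- In the mixed models of section 14.2, add treatment-by-sex and treatment-by-sex-by-time. The second term is needed because a sex difference may appear in the course over visits. Take sex-specific estimates from these models in place of the separate ANOVAs.
- Keep the sex-specific Kaplan-Meier curves as descriptive figures.
- Label all of this exploratory, and state that a sex difference will not be inferred from significance in one sex alone.

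The cost is a change of wording in the analysis sections; no extra data, visits or participants are needed. The drawback is the low power of the interaction, so a non-significant result must not be reported as evidence that the sexes respond alike.

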***Hypothesis 1 – Clinical recovery:***

Individuals in the SAEP will have lower symptom scores and faster return to asymptomatic status, leading to shorter clinical recovery times compared to those in usual care group.

**Specific Aim 2:** To determine the effect of an SAEP in concussed subjects on ANS function, blood biomarkers, and cognition.

***Hypothesis 2a*** – Cardiovascular responses:

Compared to the SAEP, the usual of care group will display lower HRV and BPV at days 14, 21, and 28 post-SRC.

***Hypothesis 2b:*** *- Peripheral blood biomarkers:*

As compared to the usual of care group, the SAEP group will display higher peripheral concentrations of neuroreparative indices BDNF and PRDX-6, lower concentrations of the CNS-injury analogue GFAP, lower concentrations of the inflammatory marker MCP-1, and lower resting peripheral catecholamine levels.

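### Dropping biomarker values outside the quantitation limits biases a true group difference toward zero and costs power, by an amount that depends on out-of-range rates the protocol does not give

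*Protocol*

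**What the plan says.** Protocol section 14.2 plans a repeated-measures comparison for the biomarkers: "A mixed model ANOVA will be used to evaluate possible differences in symptoms, HRV, BPV, cognitive performance and blood biomarkers". It then restricts the data that enter it: "each individual biomarker will only be included for statistical quantitation if they fall within the lower and upper limits of quantitation". The restriction works sample by sample: "A quantifiable sample is 1) within the manufacturers quantitative range, and 2) displays a CV between duplicates of < 25" per cent.

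A floor decides whether means are compared at all: "mean statistical analysis will only be performed on biomarkers that have quantifiable samples in > 50%, in all groups in question". Below that floor the method changes: "In instances where one or both groups contain <50% quantifiable samples, differences between these groups will be evaluated by χ^2". The section describes no substitution or censored-data method for values outside the limits.

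Hypothesis 2b in Protocol section 8.0 gives the expected direction. With SAEP it predicts "lower concentrations of the CNS-injury analogue GFAP" and "lower concentrations of the inflammatory marker MCP-1, and lower resting peripheral catecholamine levels". BDNF and PRDX-6 are expected to be higher with SAEP. The protocol gives no biomarker effect size or SD and no expected share of samples outside the limits.

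**The concern.** An out-of-range result carries information: the concentration is below LLOQ, or above the upper limit (ULOQ). Deleting it makes inclusion depend on the value being measured. If exercise lowers GFAP, MCP-1 or catecholamines as predicted, more SAEP than usual-care values are deleted at the low end, so the mean of the retained SAEP values rises by more than the usual-care mean. For BDNF and PRDX-6, deleting high SAEP values at ULOQ or low usual-care values at LLOQ works in the same direction. The floor permits this until just under half of a group has been removed.

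A mixed model does not in general repair the bias, because deletion depends on the unrecorded value itself. Correlation between visits may soften it. At stake are the biomarker comparisons of Aim 2, where a real effect could be reported as smaller than it is or as absent. Section 14.2 also plans separate analyses by sex with about 40% females. If the 53 per group in section 13.0 is reached, that is 0.40 × 53 ≈ 21 women per group, so each lost sample counts for more.

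**Working it through.** **Inputs from the protocol.** The deletion rule, the 50% floor and the chi-square fallback (section 14.2); the direction of effect (section 8.0, Hypothesis 2b); 53 per group (section 13.0, sized for time to clearance, not for biomarkers). The protocol has no biomarker figure to reproduce.

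**Assumptions.** Normal values with SD 1 on the analysis scale (for example log concentration); usual-care mean 0 and SAEP mean −d; one time point; truncation at LLOQ only. The share f of usual-care samples below LLOQ is varied from 1% to 35%, and d is 0.3, 0.5 or 0.8.

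**Formulas.** LLOQ = Φ⁻¹(f). Share of SAEP below = Φ(LLOQ + d). Mean of the retained values in a group with mean m is m + λ, where a = LLOQ − m and λ = φ(a)/(1 − Φ(a)). Retained share = (difference of retained means)/d.

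**One case in full (d = 0.5, f = 20%).**
- LLOQ = −0.842.
- Usual care: 0 + 0.280/0.800 = 0.350.
- SAEP: a = −0.342, 36.6% below; −0.5 + 0.376/0.634 = 0.094.
- Retained difference 0.350 − 0.094 = 0.256 SD; 0.256/0.5 = 51%.

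**Across the range** (share of SAEP below LLOQ → share of the true difference retained):

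| Usual care below LLOQ | d = 0.3 | d = 0.5 | d = 0.8 |
|---|---|---|---|
| 1% | 2% → 92% | 3% → 90% | 6% → 87% |
| 5% | 9% → 77% | 13% → 74% | 20% → 70% |
| 10% | 16% → 67% | 22% → 64% | 32% → 60% |
| 20% | 29% → 54% | 37% → 51% | 48% → 47% |
| 30% | 41% → 45% | 49% → 43% | chi-square |
| 35% | 47% → 42% | chi-square | chi-square |

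Cells marked chi-square have more than 50% of SAEP samples below LLOQ, so means are no longer compared.

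**No effect.** With d = 0 both groups have the same λ, so the retained difference is 0. Deletion creates no difference.

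**Power (d = 0.5, 53 per group, two-sided 0.05).** The retained variance is 1 + aλ − λ². At f = 10% it is 0.712 in usual care and 0.565 in SAEP, with 53 × 0.90 = 47.7 and 53 × 0.783 = 41.5 samples left. The standard error is √(0.712/47.7 + 0.565/41.5) = 0.169, and power is Φ(0.3195/0.169 − 1.96) ≈ 47%. Without deletion it is 73%. At f = 5% it is 57%, and at f = 20% it is 34%.

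**Dropping against censoring (simulation, 1000 runs per cell, d = 0.5, 53 per group).**

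| Usual care below LLOQ | Dropping: difference, power | Censored likelihood: difference, power |
|---|---|---|
| 5% | 0.36 SD, 52% | 0.49 SD, 69% |
| 10% | 0.31 SD, 44% | 0.50 SD, 72% |
| 20% | 0.25 SD, 32% | 0.50 SD, 70% |

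**Other scales.** Divided by the truncated SD, the standardised difference keeps at least 62-67% within the rule (shifts of 0.2 to 0.7 SD). On an untransformed log-normal scale 57-93% of the raw difference remains over the range tried.

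**The case against.** The strongest counter-argument is about size. A reader might infer that the rule cuts the difference by half or more. The protocol does not support that, because it gives no below-LLOQ rate for any marker. At d = 0.5, halving needs about 21% of usual-care and 38% of SAEP samples below LLOQ. At 1% of usual care the loss is only 8-13%, and the standardised difference is not halved anywhere within the rule. The 50% floor also bounds the loss, since heavier truncation moves the comparison to chi-square.

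A reader might also infer that the rule could produce spurious effects. It does not: the error is conservative, a loss of sensitivity.

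A third inference, that the chi-square test certainly mixes assay failures with low or high concentrations, goes beyond the text. Section 14.2 does not say what is tabulated, and it separately excludes samples with a duplicate CV above 25%, which may be gone before any table is built. Because the definition of a quantifiable sample includes the CV condition, the mixed reading remains open. This is an ambiguity to settle.

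The figures cover LLOQ only and one visit, whereas the plan uses several visits. No separate figure was derived for ULOQ, so for BDNF and PRDX-6 only the direction is argued. A censored mixed model also rests on a distributional assumption.

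These points limit the size of the claim. They leave the mechanism, its direction and the remedy untouched. A separate analysis plan may exist, but the criticism is of a rule the protocol states, not of a missing detail.

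**Conclusion.** The rule in section 14.2 biases a true difference in the direction of Hypothesis 2b toward zero and loses power. Under the stated assumptions and shifts of 0.3 to 0.8 SD, the surviving share runs from about 92% when truncation is rare to about 42-43% near the edge of the 50% rule (d = 0.3 with 35% of usual care below LLOQ; d = 0.5 with 30%). Confidence is high in the direction. The size is conditional on out-of-range rates that the protocol does not state. The biomarkers are secondary outcomes and the primary analysis of time to medical clearance is untouched, so this is a change that should be made, not one on which the trial depends.

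**What to change.** In Protocol section 14.2:

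1. Keep out-of-range biomarker values, as left-censored at LLOQ or right-censored at ULOQ, in a censored-data mixed model (for example Tobit-type) on the log scale.
2. Drop a sample only for technical failure, that is, a duplicate CV above 25%.
3. If the chi-square fallback is used, state that it tabulates out-of-range against in-range values among samples that pass the CV check.

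This needs no new participants, samples or visits. It costs somewhat more analysis work and adds reliance on a distributional assumption. Estimates may be unstable in the sex-specific subsets: with about 21 women per group and 37% of SAEP values below LLOQ, only 21 × 0.63 ≈ 13 observed values remain in the SAEP group. A Tobit-type model is one of several suitable censored-data methods.
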